## Sampling Phase

The goal of the two-week Sampling Phase is for participants to become familiar with the study product and choose the nicotine concentration and flavor(s) they will use to attempt to switch to during the first part of the Switch Phase. Additionally, as our prior research demonstrates product sampling is particularly important in supporting smoking cessation success among rural smokers,^70^ the Sampling Phase is intended to strengthen switching outcomes in the Switch and Observation Phases.

Study Products provided during the Sampling Phase (sent to participants in their study kits based on their randomization) include Zyn brand oral nicotine pouches (ONPs) and Nicotine Replacement Therapy (NRT) lozenges and patches.

Oral Nicotine Pouch (ONP) group participants will receive ONP products in up to three flavors (selected via their baseline questionnaire) for the 2-week Sampling Phase: 3mg and 6mg nicotine concentration in each chosen flavor. We will instruct participants to start with lower nicotine concentration pouches and to only escalate to higher nicotine concentration pouches if they are not experiencing adverse effects (e.g., dizziness, nausea). Participants who wish to try the higher nicotine concentration pouches will also be encouraged to try them first for shorter time periods (e.g., 10 minutes) before committing to a full 30- to 60-minute use session.

Nicotine Replacement Therapy (NRT) group participants will receive NRT patches and lozenges. NRT lozenges were selected as an active control condition because they are FDA-approved, available for purchase without a prescription, and have demonstrated efficacy in helping smokers quit.^60^ We will include the initial 2-week provision of 2mg and 4mg lozenges and 14mg and 21mg patches (Rugby brand) for trial during the Sampling Phase. As with ONP instructions, participants will be instructed to start with the lowest nicotine dosages of NRT and to only escalate to higher nicotine concentrations (for shorter time periods to start) if they do not experience adverse effects.

The Sampling Phase will include two calls with study staff, a brief messaging contact halfway through and a self-administered survey, with iCO measurement, at the end of the sampling phase.

Sampling Phase: Pre-Sampling Zoom/Call

The Pre-sampling Zoom or phone call will be scheduled for when participants have received their study kits. Reminders about the call will be sent 1-2 days before the scheduled Pre-Sampling Call ***(PreSamp Call Reminder Text, Zoom Instructions Reminder Email).*** The Zoom/call will include study product education, use instructions, and troubleshooting tips. Participants will also complete their first iCO measurement during the pre-sampling call. This measurement will confirm that they are smoker. If the measurement is ≥7 ppm, they will be considered a smoker. If the measurement is less than 7 ppm, they will not be able to participate. During this call, participants will also verbally confirm that they are not pregnant.

Participants will set an agreed upon switch date approximately 2 weeks from the pre-sampling call and will be asked to immediately start using their sample products ad libitum to become familiar with their use. Participants will also be informed that they will receive two additional product shipments, one before their switch day and another ~6 weeks after their switch day. Participants will be asked prior to future shipments what flavors and nicotine concentrations they would prefer to be sent. ***(Pre-sampling Call Script).***

Sampling Phase: Product Sample Survey

The Sampling Phase check-in message/questions will be automatically sent via REDCap (text or email) 6-7 days after the Pre-Sampling Call. The questions will ask participants to choose study product nicotine concentration(s) and flavor(s) for the first ~6 weeks of the Switch Phase. ***(Product Sample Survey)*** If the questions are not completed in 24 hours, the study team will follow-up with a phone call and text and/or email ***(Survey reminder).*** Study staff will call, email or text (any combination based on participant preferences) participants up to 10 times to remind them to complete the survey if they have not completed it within two weeks. The switch phase may be delayed if the participant has a delayed response to the survey.

Sampling Phase: Post-sampling Survey

The Post-sampling Survey will assess participants’ confidence in switching to their study product, as well as their experiences and extent of sampling during the Sampling Phase ***(Survey Message, Post-Samp Survey****)*. The post-sampling survey will be sent on day 10 after the sampling phase starts. The survey will be completed prior to the Post-Sampling Call. Study staff will call, email, or text (any combination based on participant preferences) participants up to 10 times to remind them to complete the survey if they have not completed it within two weeks. ***(Survey reminder).***

Sampling Phase: Post-sampling Call

The Post-sampling Call will be one to two days before the participant’s switch date. Study staff will confirm receipt of additional products, remind participants of their switch date and that upon waking the morning of their Switch Date they should not smoke cigarettes. They will be instructed to stop smoking and continue with their allocated study product (ONP or NRT) for 12 weeks. Staff will also answer any product use questions and provide troubleshooting as needed. ***(Post-Samp Call Script)*** If study staff are unable to connect with the participant, the participant will be emailed or texted the information ***(Post-Samp Email).***

## Switch Phase

The Switch Phase will start on a participant’s “switch date” and will last for 12 weeks. Study participants will receive a reminder text the day before and on the day of their Switch Day ***(SD Reminder Text).*** The goal of the Switch Phase is to identify whether there are differences in cigarette smoking patterns (i.e., switching to the study product, abstinence from cigarettes, and frequency of smoking) between the ONP and NRT groups. We will also assess potential differences in subjective measures of product appeal, craving and withdrawal relief, and changes in perceived cigarette dependence between groups.

Switch Phase: Product Sample Survey

The Switch Phase product sample survey will be automatically sent via REDCap 4 weeks after switch day. ***(Product Sample Survey).*** Participants will be asked to complete questions on their study product preferences for nicotine concentration and flavor for their next (and last) product shipment. Study staff will call, email or text (any combination based on participant preferences) participants up to 10 times to remind them to complete the survey if they have not completed it within two weeks. ***(Survey Reminder)***

Switch Phase: Mid-Switch Survey

The Mid-Switch Survey will be self-administered via REDCap 6 weeks after the switch date to assess product appeal, craving and withdrawal, perceived cigarette dependence, and smoking and study product use behaviors; this survey will also include an iCO assessment. ***(Survey Message, Mid-Switch Survey)*** Study staff will call, email or text (any combination based on participant preferences) participants up to 10 times to remind them to complete the survey if they have not completed it within two weeks. ***(Survey reminder).***

Switch Phase: Mid-Switch Phone Call

The Switch Phase Mid-Switch Phone Call will occur approximately 6 weeks after the switch date, after participants have received their product shipment. This call will provide an opportunity to check-in with participants to confirm receipt of their final shipment and answer any product- or study-related questions. Participants will also be reminded about completing the Switch Phase assessment survey that occurs at the end of Switch Phase (12-weeks after switch date). ***(Mid-Switch Phone Call Script)*** If study staff are unable to connect with the participant, the participant will be emailed or texted the information ***(Mid-Switch Email).***

Switch Phase: Post-Switch Survey

The Post Switch survey will be self-administered via REDCap 12 weeks after the switch date to measure product appeal, craving and withdrawal, perceived cigarette dependence, and changes in smoking patterns (e.g., abstinence from cigarettes, frequency of smoking, use of the study product). The Switch Phase assessment survey will also measure iCO. ***(Survey Message, Post-Switch Survey*)** Study staff will call, email or text (any combination based on participant preferences) participants up to 10 times to remind them to complete the survey if they have not completed it within two weeks. ***(Survey reminder).***

## Observation Phase

The Observation Phase will begin immediately after the Switching Phase and will last for 14 weeks. The goal of the Observation Phase is to assess changes in smoking and sustained use of study products when they are no longer provided for free. Secondary goals will include assessing changes in nicotine concentrations, flavors, and brands used, as well as uptake of the other nicotine/tobacco products. This phase will help us to continue to track any adverse events that may occur following use of the study products.

Observation Phase: Survey

Participants will complete a survey at the end of the Observation Phase. ***(Survey Message, Observation Survey)*** The Observation Phase Survey will measure smoking and product use outcomes as described in the previous paragraph, including an iCO assessment. It will be delivered via REDCap and participants will receive several automated notifications to complete the survey. Study staff will also call, email, or text (any combination based on participant preferences) participants up to 10 times to remind them to complete the survey if they have not completed it within two weeks ***(Survey reminder).***

Observation Phase: Phone Call

After the survey is submitted, participants will receive a debriefing call. ***(Debrief Call Schedule Reminder)*** During the Debriefing Call, participants who report continued cigarette smoking will be strongly advised to quit smoking and will be emailed cessation resources ***(Cessation Resources).*** Those who have completely switched to ONPs or NRT will be encouraged to continue not smoking cigarettes and will be emailed cessation resources to assist with quitting all nicotine. ***(Debrief Phone Call Script)*** If we are unable to reach the participant by phone, they will receive a debrief email ***(Debrief Email).***

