**Research Design**

We will use a 6-month, two-arm, remote randomized switching trial of 1,000 smokers living in rural Appalachia. After randomization to the ONP or NRT (patch and lozenge) arm, during a 2-week Sampling Phase, participants will be sent ONPs or NRT in varied flavors and nicotine concentrations. Participants will sample and familiarize themselves with use of their study product and will select a nicotine concentration and flavor to use for the switch phase. During the 12-week Switch Phase, participants will attempt to stop smoking cigarettes and entirely switch to their study ONP or NRT. During the 14-week Observation Phase, participants will no longer receive study products but will be followed to evaluate longer-term switching outcomes. Throughout the trial, self-reported changes in cigarette smoking via online surveys will be confirmed using remote carbon monoxide assessment.

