Aim 3: Aim 3 will examine differences between the ONP and NRT arms in (H3a) abstinence from cigarettes, (H3b) number of days the study products are used, and (H3c) purchase and continued use of the study products during the 14-week Observation Phase. Hypothesis 3a: The analysis of abstinence from cigarettes at the end of the Observation Phase will mirror that of hypothesis 1b and will be evaluated with a logistic regression model. Hypothesis 3b: Linear regression analysis will be used to compare the number of days the products are used during the Observation Phase between the ONP and NRT arms; a normalizing transformation will be employed if needed and appropriate baseline characteristics will be adjusted for. Hypothesis 3c: The continued purchase and use of either ONP or NRT after during the 14-week Observation Phase will be compared between the arms with logistic regression analysis, adjusting for all appropriate confounders. Missing Data: In the event of missing data, we will contact participants immediately. If a participant drops out, we will attempt to gather follow-up information by calling and trying to reach the participant through other provided contact information. However, if a participant refuses to be contacted or loses contact with the investigators, we will censor data at point of loss. Two statistical approaches will be used to handle missing data. First, we will use inverse probability weighting with propensity scores. This is a two-step procedure in which we first model the probability of missingness as a function of baseline covariates and previous outcomes. Next, the inverse of the resulting predicted probabilities (from the logistic regression model) will serve as weights in our proposed model of the response. We will compare these results to a more conservative intent-to-treat approach as a final step.

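### H3b counts days of product use in the Observation Phase whatever the source, so leftover free product may be mixed with bought product when the phase is meant to show use without free supply

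*Protocol*

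**What the plan says.** The goal of the Observation Phase (Protocol section 3, Observation Phase) is to "assess changes in smoking and sustained use of study products when they are no longer provided for free". There is no gap before it: "The Observation Phase will begin immediately after the Switching Phase and will last for 14 weeks". Research Design says that in this phase "participants will no longer receive study products but will be followed to evaluate longer-term switching outcomes". That ends new supply and is silent on product already in the home.

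After the sampling kit, participants are told that "they will receive two additional product shipments, one before their switch day and another ~6 weeks after their switch day" (Sampling Phase, Pre-Sampling Zoom/Call). The contents of the last shipment depend on a preference survey: "The Switch Phase product sample survey will be automatically sent via REDCap 4 weeks after switch day". It asks about strength and flavor "for their next (and last) product shipment". No quantity per shipment is given. The one stated use pattern, for the Sampling Phase, is to "immediately start using their sample products ad libitum to become familiar with their use".

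The H3b analysis (section 15, Aim 3) is a linear regression to "compare the number of days the products are used during the Observation Phase between the ONP and NRT arms". Neither that text nor the H3b hypothesis in section 2 sets a condition on source. H3c is purchase alone in section 2, but purchase together with ongoing use in section 15, with no rule for combining the two.

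**The concern.** The phase goal and the H3b endpoint do not fully match. The goal is use after free supply has ended. The endpoint is any use after a calendar date, week 12. A participant still working through study product after that date scores the same on H3b as one who buys it. The use component of H3c in section 15 has the same weakness. The purchase component is affected differently: someone with stock in hand has less reason to buy, so purchase may come later or not at all.

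Aim 3 is where the trial asks whether either product lasts once the study stops supplying it. Stock and source are facts about a moment in time. If they are not asked at week 12 and at the final survey, no later analysis can recover them, so this cannot simply be left to a statistical analysis plan.

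The timetable adds a foreseeable route to carry-over. The preference survey for the last shipment goes out at week 4, and the only staff follow-up described is for participants who have not answered within two weeks. Yet the mid-switch call at about week 6 assumes that the shipment has arrived. The first preference survey, in the Sampling Phase, is followed up after 24 hours, and the start of the Switch Phase may be moved for a late answer. The second survey has neither safeguard.

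**Working it through.** **1. The plan's own figures.** The protocol gives no power, standard deviation (SD) or effect size for H3b or H3c. Its power statements (section 15) concern abstinence, 13% vs 23%, two-sided α = 0.05. With pooled variance under the null, power = Φ{[0.10 − 1.96·√(2·0.18·0.82/n)] / √[(0.13·0.87 + 0.23·0.77)/n]}. This gives 95.9% at n = 400 per arm and 93.3% at n = 350, in line with the stated figures of over 95% and over 90%. These are sound, but they say nothing about days of use.

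**2. Length of the phase.** 14 weeks × 7 = 98 days, the upper limit of H3b.

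**3. Timing of the last shipment.** Survey at week 4 + 2 weeks = week 6 for the staff follow-up that is described, the same week in which the shipment should already be in hand. A participant who answers only after that follow-up cannot meet the planned date.

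**4. Possible carry-over.** Assumption, not in the protocol: each Switch Phase shipment holds 42 days of product. Days left at week 12 = 42 × (1 − share used).

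| Share used by week 12 | Left from last shipment | Share of 98 days | Left if the same share applies to both Switch Phase shipments (84 days) | Share of 98 days |
|---|---|---|---|---|
| 100% | 0 days | 0% | 0 days | 0% |
| 75% | 10.5 days | 11% | 21 days | 21% |
| 50% | 21 days | 21% | 42 days | 43% |
| 25% | 31.5 days | 32% | 63 days | 64% |

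With full use but late arrival, days carried over = 7 × weeks late: one week gives 7 days (7/98 = 7%) and two weeks give 14 days (14/98 = 14%). The protocol does not allow an estimate of how many participants fall in any row.

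**5. What an unequal carry-over could do.** Assumptions: no bought use in either arm, 350 per arm (the protocol's expected number at the end of this phase), and an SD of 20 to 40 days. The chance of a significant difference is about Φ{δ / [SD·√(2/350)] − 1.96}, where δ is the gap between arms in mean days used from leftover stock. For δ = 5 and SD = 20: 5 / (20 × 0.0756) = 3.31, and Φ(1.35) = 91%. For SD = 40: 1.65, and Φ(−0.31) = 38%.

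| Gap δ | Chance of p < 0.05, SD 40 to SD 20 |
|---|---|
| 3 days | 17% to 51% |
| 5 days | 38% to 91% |
| 7 days | 64% to 99.6% |

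With equal leftovers (δ = 0) the means rise by the same amount and no false difference arises.

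**The case against.** The strongest reply is that nothing in the text is contradictory. Supply does stop at week 12, H3b is defined as use and not as bought use, and payment has its own outcome in H3c. The Post-Switch Survey, the Observation Survey and the procedure manual are named but not shown, and they may already ask about source or remaining stock. The planned receipt of the last shipment is about week 6, with a call to confirm it. The two-week wording may also not fix the first staff contact: in the Sampling Phase the same sentence stands beside a 24-hour follow-up.

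Much of this stands. It limits the point to a risk that the protocol leaves open. It does not remove the mismatch, because H3b as defined ignores source while the phase goal does not, and for the second preference survey no earlier follow-up is described.

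A reader might infer more than the documents support:

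- **That free product is known to carry over.** No quantity and no expected leftover is stated, so the day counts above are illustrations.
- **That H3c as a purchase outcome is miscounted.** Using old stock is not a purchase. Stock can only delay or lower purchase.
- **That the comparison is biased in a known direction.** Patch plus lozenge against pouches, and the appeal hypothesis H2a, make unequal leftovers plausible, but they give neither sign nor size.
- **That H3b should therefore count only bought product.** A participant using leftovers would then score zero on those days, which penalises the arm with more stock and could reverse the bias.

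**Conclusion.** The concern holds in a limited form. As written, H3b and the use component of H3c in section 15 may mix free and bought product, and the protocol describes no step to tell them apart. Under an assumed 42-day last shipment, plausible cases amount to 14 to 21 of 98 days (14% to 21%) for an affected participant. The number affected is unknown. The effect on the arm comparison depends entirely on whether leftovers differ by arm: a mean gap of 5 days could produce a significant result 38% to 91% of the time under the assumptions in the working, and no gap would produce none. The primary outcome (verified abstinence at week 12) and Aims 1 and 2 are untouched. The change is worth making because it is cheap and the information cannot be recovered later.

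**What to change.** - **Data.** If not already asked, add to the week-12 survey the amount of each free study product still held. Add to the Observation Survey the source of product used (left over from the study or obtained elsewhere) and the date of first purchase.
- **H3b.** Keep all-source days as the endpoint. Prespecify a sensitivity analysis restricted to days on product obtained outside the study, or to days after free stock ran out. Read the two together: all-source days count a leftover day in full, and outside-product days count it as zero.
- **H3c.** Make sections 2 and 15 agree on whether the outcome is purchase alone or purchase with use and, if both, how they combine. Do not adjust for week-12 stock, which arises after randomization and may itself differ by arm. Report stock by arm descriptively.
- **Timing.** Start staff follow-up of the week-4 preference survey at 24 hours, as for the first one, so that the last shipment can arrive by about week 6 as the mid-switch call assumes.

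The cost is a few more survey items, reliance on self-reported source, and slightly more staff contact.

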## Data Collection and Management

Across all aims, data will be collected and stored electronically in the secure database, REDCap. Data will only be accessible to approved study personnel and will be secured through multiple firewalls. Subjects’ first and last names will be deidentified and not linked with the data. The consent forms with first and last names will be stored electronically in REDCap but will not be downloaded with any study data. Survey data will be collected via REDCap on participants electronic devices.

Leveraging REDCap for survey links will reduce the possibility of study staff errors.

## Procedure Manual

Study procedures, collecting iCO measurements, completing and logging phone calls, assembling and shipping kits, gift card administration, and other procedures will be thoroughly explained in the study procedure manual.

### Obtain exhaled iCO

iCO measurements will be collected according to the participant iCO Instructions at timepoints throughout the Baseline, Sampling, Switching, and Observation phases.

Bedfont iCO Smokerlyzer monitor (Bluetooth version) will measure exhaled CO levels and

biochemically confirm smoking status over the course of the study. Participants will be prompted to connect the iCO device to their phone following completion of each assessment and provided step-by-step directions on how to complete the test. Results will be date and time stamped and saved. Our CO criteria for smoking abstinence is consistent with numerous other studies using cutoffs of ≤ 6 ppm.^87–92^ As ONPs and NRT do not produce CO, exhaled CO is a valid indicator of smoking status and compares favorably with cotinine and other biochemical measures that have longer detection windows.^93–96^ Self-reports of abstinence combined with CO levels suggestive of recent abstinence provide an accurate, immediate, and practical measure of abstinence from cigarettes. The manufacturer indicates that the iCO is valid for approximately 200 CO tests and has a sensor sensitivity of 1 ppm.^97^ Our protocol will require no more than 5 CO testing sessions—well within the defined valid use range.

